### Outpatient service use

As decreased hospitalizations are often linked with increased outpatient service use, we expect that HEVs who receive CTI will have increased engagement with outpatient VA mental health, SUD, primary care, and vocational services and decreased emergency department (ED) use. We will use VA administrative data to compare the use of these services (Table 3) among HEVs in aftercare with diagnoses indicating that they would benefit from such care at sites receiving REP versus enhanced REP, as well as implementation versus control sites.

Using these same comparison groups, we will assess differences in primary care engagement using established VA benchmarks (i.e., primary care provider assignment and having ≥1 visit/year). For all HEVs noted in the aftercare roster to be seeking employment, we will assess the use of VA vocational services. For HEVs with mental health disorders or SUDs noted by the International Classification of Diseases (ICD)-10 codes associated with inpatient and outpatient VA care, we will assess and compare their engagement with outpatient mental health and/or SUD services, respectively (i.e., the total number of visits, number of quarters with ≥1 visit).

### HEV and case manager experiences

We will conduct semi-structured interviews with HEVs at implementation sites at baseline and 18 months, characterizing and comparing HEVs’ experiences of and satisfaction with aftercare pre- and post-CTI implementation. We will use semi-structured interviews with aftercare staff at implementation sites (at baseline and 12 months) to characterize case manager experiences with REP and/or enhanced REP and experiences of and satisfaction with providing aftercare services pre- and post-CTI implementation. We will assess for differences in staff experiences between sites that received REP versus enhanced REP. Data from these interviews will be integrated with periodic reflections to assess contextual factors and implementation strategy components associated with the valence of experiences described by HEVs and case managers.

### Costs and return-on-investment (ROI)

We will estimate the costs and ROI of CTI implementation in aftercare from the perspective of VA; costs associated with non-VA homeless and healthcare services are outside the scope of these analyses. We will compare costs at sites that receive REP versus enhanced REP and calculate the ROI of CTI implementation, as compared to control sites. In addition to implementation costs, CTI may lead to increased VA costs associated with enhanced outpatient service use but decreased costs associated with inpatient care. There may also be decreased costs from VA homeless services as veterans retain permanent housing.

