### Housing stability and hospitalizations

We will assess housing stability and hospitalizations among HEVs during and after receiving aftercare services, comparing: (a) REP versus enhanced REP sites and (b) the 32 implementation sites with a control group of 32 sites that did not implement CTI, matched on geographic setting and number of case managers. We will use administrative data (from VA’s Corporate Data Warehouse [CDW] and homeless registry) to assess these outcomes (Table 3).

**Table 3 Tab3:** Summary of quality metrics assessed using VA administrative data

Domain	Quality metric
Housing stability	• Number of days between aftercare entry and first VA indicator of housing instability^a^ • Annual number of encounters with VA homeless services • Annual number of discrete episodes^b^ of engagement with VA homeless services
Hospitalizations	• Number of days between aftercare entry and first hospitalization (VA or non-VA) • Annual number of hospitalizations (total and separated into medical/surgical versus mental health) • Annual number of hospital bed days
Outpatient service use	• Primary care provider assignment (yes/no) • Presence or absence of at least one primary care visits/year • Use of VA vocational services (among HEVs seeking employment) • Total number of mental health visits (among HEVs with mental health disorders) • Total number of substance use disorder treatment visits (among HEVs with substance use disorders)

^a^Use of VA homeless services

^b^New episodes desfined by 30 days passing between encounters

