Similarly, we will determine, for each HEV, the days between entry into aftercare and hospitalization (at the VA or paid for by VA at an outside hospital) and describe the time to hospitalization using Kaplan-Meier curves. We will include all hospitalization types (mental health, medical/surgical), analyzing the time to any hospitalization and by type. We will also assess for independent associations between these outcomes and implementation strategy and CTI fidelity using Cox proportional hazards models. Additional secondary outcomes will be the annual number of hospitalizations (total and by type) and the number of bed days per HEV. We will also assess time trends in housing stability and hospitalizations within implementation sites, comparing pre- and post-implementation.

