#### ROI of CTI and implementation strategies

The financial ROI of CTI and these implementation strategies depends on savings reaped through improved housing stability and decreased hospitalizations. To calculate the degree of cost offsets, we will link HEVs’ use of VA housing and health services to the costs of these activities which are available in an activity-based cost allocation system (the Managerial Cost Accounting System) [28]. Among HEVs who enroll at implementation sites between 6 and 18 months after the initiation of CTI implementation, we will calculate mean housing and health services costs per HEV in the 6, 12, and 18 months after enrollment. We will use a multivariable generalized linear model and two-part regression models where appropriate to compute ROI at 6-, 12-, and 18-month time horizons for HEVs in sites that received REP versus enhanced REP, and compared to the 32 control sites. We will compare model fit using a generalized linear model and ordinary least squares [29].

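### VA-paid stays at outside hospitals count as hospitalizations, but the cost rules as worded leave their cost out of the ROI, at odds with the stated VA perspective

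*Protocol article*

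**What the plan says.** Four places in the protocol article bear on this.

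- **Outcome, text** (*Housing stability and hospitalizations*). Time is counted from aftercare entry to "hospitalization (at the VA or paid for by VA at an outside hospital". Payment by VA therefore brings an outside stay into the outcome.
- **Outcome, Table 3** (same section). The metric is "Number of days between aftercare entry and first hospitalization (VA or non-VA". The section takes these outcomes from VA administrative data.
- **Cost scope** (*Costs and return-on-investment (ROI)*). Costs and ROI are estimated from VA's perspective, and the same sentence adds that "costs associated with non-VA homeless and healthcare services are outside the scope of these analyses".
- **Cost offsets** (*ROI of CTI and implementation strategies*). The return "depends on savings reaped through improved housing stability and decreased hospitalizations". To value it, the team links veterans' "use of VA housing and health services to the costs of these activities which are available in an activity-based cost allocation system". The same paragraph adds that "we will calculate mean housing and health services costs per HEV in the 6, 12, and 18 months after enrollment", this time without a VA qualifier.

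**The concern.** The event definition and the cost scope use the same label for what may be different things. Table 3 applies non-VA to hospital stays that, according to the text of that section, VA pays for. The cost section then excludes non-VA healthcare. An analyst who carries the term from one section to the other will count a VA-paid outside stay as a hospitalization and give it no cost.

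That would not fit the declared perspective, because VA bears the cost. Fewer hospitalizations are one of the two sources of savings named for the ROI, and *Business case analysis* (Table 5) lists them as a cost offset. Leaving out part of VA's inpatient spending would misstate that offset in the comparison of REP with enhanced REP and in the comparison of implementation with control sites. Two analysts working from this text could also build different inpatient totals.

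**Working it through.** The article gives no figure for outside stays or their cost, so there is none to reproduce. The check compares the wording and then applies simple algebra to an assumed share.

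**Step 1: what non-VA means where the article shows it.** The text of *Housing stability and hospitalizations* names two kinds of stay: at VA, or at an outside hospital with VA paying. Table 3 gives the pair for the same outcome as VA or non-VA. Matching the two, non-VA is the outside stay that VA pays for. The label describes who provides the care, not who pays.

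**Step 2: apply that meaning to the cost rules.** The cost section excludes non-VA healthcare. The ROI section links only the use of VA housing and health services to unit costs, and names one system as the source. With the meaning from step 1, both sentences leave out the VA-paid outside stay.

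**Step 3: apply the other meaning.** If non-VA in the cost section means care that VA does not pay for, the exclusion does not reach these stays. The ROI sentence must then be read as also covering services that VA buys, which it does not say.

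| Reading of non-VA in the cost section | Counted as a hospitalization | Cost included |
|---|---|---|
| Provider sense, as in Table 3 | Yes | No |
| Payer sense | Yes | Yes, if the ROI sentence is read widely |

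**Step 4: size under the provider sense.** Let C0 and C1 be VA's true mean inpatient cost per veteran in the comparison and index groups. Let s0 and s1 be the shares of that cost from VA-paid outside stays.

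- True offset = C0 − C1.
- Costed offset = (1 − s0)·C0 − (1 − s1)·C1.
- With s0 = s1 = s, costed offset = (1 − s)·(C0 − C1), so the inpatient offset is understated by the fraction s.

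| s (assumed) | Part of the inpatient offset retained | Understated by |
|---|---|---|
| 0 (same result as the payer sense) | 100% | 0% |
| 10% | 90% | 10% |
| 20% | 80% | 20% |
| 30% | 70% | 30% |

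**Step 5: unequal shares.** Suppose the true costs are equal, C0 = C1. With s1 = 20% and s0 = 30%, the costed means are 0.80 and 0.70 of the true cost. The index group then appears 0.80/0.70 − 1 = 14% dearer. With the shares exchanged, it appears 1 − 0.70/0.80 = 12.5% cheaper. The article gives no reason to expect one pattern over the other.

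**The case against.** The strongest reply is that the cost sentence opens by declaring VA's perspective, and the exclusion follows as its elaboration. Under a payer perspective, a stay that VA pays for is a VA cost, so non-VA services are naturally those VA does not fund. Other passages fit that view. The cost section speaks of lower inpatient costs without restriction, and Table 5 limits housing services to VA but does not limit hospitalizations. The named cost system, or a file linked to it, may also hold purchased care. This cannot be settled from the article, and an article may leave cost sources to a fuller document.

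Much of this stands. The payer reading is possible, and under it the distortion is nil. The absence of a named source for purchased care is not itself a fault. But the reply does not remove the conflict between sentences that are on the page. It needs non-VA to exclude VA-paid stays in the cost section when Table 3 uses it for exactly those stays, and it leaves unexplained why the ROI sentence costs only VA services.

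Two stronger readings are tempting and unsupported. A reader might infer that the plan sets the cost of these stays at zero as a rule; no sentence says so. A reader might also infer a bias against CTI or enhanced REP, on the ground that better linkage moves stays from outside hospitals to VA hospitals. *Outpatient service use* predicts more engagement with outpatient VA services only, and nothing in the article predicts a shift in where inpatient stays occur.

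**Conclusion.** The point holds as a mismatch of scope. Followed in its own vocabulary, the article counts VA-paid outside stays as hospitalizations and leaves their cost out of an ROI taken from VA's perspective.

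The effect ranges from nil, if the payer sense was meant, to an understatement of the inpatient offset by the outside share s. That result assumes the same s in every group, and the 10% to 30% used above is illustrative. If s differs between groups, neither the direction nor the size can be predicted. The percentages apply to the inpatient offset, not to the whole ROI, which also depends on housing services, outpatient care and implementation costs.

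The correction is worth making before costs are assembled. It concerns a secondary cost and ROI analysis and does not touch CTI fidelity, the primary outcome.

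**What to change.** In *Costs and return-on-investment (ROI)* and *ROI of CTI and implementation strategies*:

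1. Define the VA perspective as all costs that VA bears.
2. Cost VA-paid stays at outside hospitals at the amount VA paid, and add them to the services costed from the named system.
3. Exclude only care that VA does not pay for, and replace the term non-VA with that description.
4. Use the same set of stays for the hospitalization outcome and the inpatient cost offset, and word Table 3 to match.

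If payment amounts cannot be obtained, the weaker alternative is to exclude these stays openly and report a hospitalization outcome limited to VA hospitals beside the ROI.

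The cost is a change of wording and a small amount of data linkage, since the outcome definition already requires the trial to identify these stays. No new sites or participants are needed.

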#### Assessing CTI costs as actually implemented

The predominant cost of delivering CTI in aftercare is case manager time. Case managers are funded by the GPD National Program Office; we anticipate that case managers’ activities will be reorganized to deliver CTI, increasing their efficiency without additional costs. To test this, we will compare the mean monthly cost of CTI case management per aftercare HEV served to the mean monthly cost at aftercare control sites.

We will obtain estimates of case manager salary and benefits from the GPD National Program Office. Then, using a roster of HEVs at each aftercare site, we will determine the average number of HEVs served per case manager per month between 6 and 18 months post-CTI implementation. For each case manager, we will calculate the cost per HEV served per month, comparing implementation versus control sites. In addition, data from 12-month aftercare staff interviews will be used to glean contextual factors that may influence caseload and case management activities.

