## Abstract

**Background:**

The Veterans Health Administration (VA) Grant and Per Diem case management “aftercare” program provides 6 months of case management for homeless-experienced veterans (HEVs) undergoing housing transitions. To standardize and improve aftercare services, we will implement critical time intervention (CTI), an evidence-based, structured, and time-limited case management practice. We will use two strategies to support the implementation and sustainment of CTI at 32 aftercare sites, conduct a mixed-methods evaluation of this implementation initiative, and generate a business case analysis and implementation playbook to support the continued spread and sustainment of CTI in aftercare.

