### CTI implementation pilot

Housing Transitions QUERI builds on a 1-year implementation pilot in which we developed resources and processes for CTI training and technical assistance (TA) and external facilitation that were piloted and refined at four aftercare sites. We also identified outcome measures for future evaluation. To this end, we formed a virtual stakeholder workgroup comprised of two CTI expert trainers, a faculty consultant from a university-based center with CTI expertise, a VA social worker who served as the “liaison” to the four pilot sites, and a peer provider with professional and lived expertise in GPD programs.

We drew upon this workgroup to tailor a 6-month version of CTI that was previously implemented in Connecticut-based homeless programs [17]. We made practice adaptations to reflect the aftercare context and augmented anonymized cases presented in the training and TA materials to reflect the social circumstances, functioning, and diagnoses of HEVs in aftercare. We made additional adaptations in response to precautions imposed by the coronavirus disease 2019 (COVID-19) pandemic and ensured that all training and TA could be delivered virtually. We also developed an online toolkit [18] with clinical resources, recorded trainings, a CTI manual, and training and TA slide decks.

Next, we pilot-tested this adapted training and TA package (Table 1) with aftercare case managers, supervisors, and our VA social work liaison. First, initial CTI training was delivered in six synchronous videoconferences by national leaders in training and consultation for case managers serving homeless-experienced adults. Next, we initiated a monthly community of practice sessions, i.e., 1-hour discussions to deepen knowledge and expertise in CTI; these sessions included a presentation from the community of practice leader (a social worker on our team) or guest speaker, followed by a moderated discussion among aftercare staff. We also offered individual, on-demand, 30-min case consultations to aftercare staff with a CTI-trained clinician expert on our team.

**Table 1 Tab1:** CTI training and technical assistance (TA) package tailored in the Housing Transitions QUERI implementation pilot

Training/TA component	When is the component delivered?
Six session initial CTI training delivered via synchronous videoconference (2 h/week for 6 weeks)	Once, at the start of CTI implementation, for all aftercare case managers and supervisors

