### Business case analysis

We will use findings from our implementation evaluation to prepare a business case analysis of the costs, cost offsets, and non-financial benefits of CTI sustainment and spread in aftercare and the business case for REP versus enhanced REP. These analyses will be prepared from the perspective of VA’s Homeless Program Office, which oversees aftercare and pays for its services. Table 5 displays expected CTI costs (for spread/sustainment and care delivery) and benefits (cost offsets and non-financial evaluation). Our evaluation estimates the magnitude and features of these costs and benefits. We will assess whether enhanced REP’s investment in EF yields a sufficient combination of downstream financial cost offsets and non-financial benefits to justify enhanced REP as the preferred strategy, over REP alone, to spread and sustain CTI. We will also provide information about aftercare contextual factors that may signal an above-average benefit from enhanced REP versus REP.

**Table 5 Tab5:** Expected resources and benefits to be measured for CTI spread and sustainment

Expected resources (costs)		Expected benefits
Spread/Sustainment costs	Care delivery costs	Cost offsets and non-financial benefits
• *Fixed*: Implementation team providing 6-week CTI training, aftercare staff and VA aftercare liaison receiving a 6-week CTI training, Community of Practice webinars, toolkit maintenance, and quarterly CTI booster sessions • *Variable*: Implementation team and aftercare staff time spent giving/receiving case consultation and EF^a^	• *Variable:* Aftercare staff time spent providing CTI^b^; VA provider time associated with increased outpatient mental health, SUD, medical, and vocational service use	• *Cost offset:* decreased use of VA residential housing services; decreased hospitalizations • *Non-financial benefits*: HEVs’ housing stability; HEVs’ receipt of needed mental health, SUD, medical and vocational services; improved HEVs’ care experiences; improved case managers’ experiences providing care

^a^Only applies to aftercare sites receiving enhanced REP to support CTI implementation and sustainment

^b^If there are additional costs associated with using CTI and/or the policy partners were to stop paying for this staff

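### Monthly case management cost per HEV cannot separate more veterans served from the same veterans kept longer; cost per HEV entering and mean stay should be reported beside it

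*Protocol article*

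**What the plan says.** In the protocol article, the section on assessing CTI costs as actually implemented expects case managers' work to be reorganised around CTI, "increasing their efficiency without additional costs". It then names the test of that expectation: "we will compare the mean monthly cost of CTI case management per aftercare HEV served to the mean monthly cost at aftercare control sites".

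Both parts of the ratio are specified. For the numerator, "We will obtain estimates of case manager salary and benefits from the GPD National Program Office". For the denominator, "we will determine the average number of HEVs served per case manager per month between 6 and 18 months post-CTI implementation". The unit of comparison is then fixed: "For each case manager, we will calculate the cost per HEV served per month, comparing implementation versus control sites". Staff interviews at 12 months add context on caseload. The section names no measure of length of stay, of cost per veteran or episode, or of case manager time.

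Two other sections depend on the result. In the business case analysis, Table 5 lists "Aftercare staff time spent providing CTI" as a care delivery cost. Its footnote b limits this item to the case where CTI brings extra cost or the partners cease to fund the staff. The ROI section costs VA housing and health services per HEV over 6, 12 and 18 months from enrolment, and does not name case manager cost.

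On duration, the Abstract says the aftercare program "provides 6 months of case management for homeless-experienced veterans (HEVs) undergoing housing transitions". The pilot section says the team set out to "tailor a 6-month version of CTI that was previously implemented in Connecticut-based homeless programs". The general description of CTI gives 6 to 9 months.

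**The concern.** A case manager's pay does not depend on how long each veteran stays. Dividing it by the number of veterans on the books in a month therefore gives a price per veteran-month, and that price moves with caseload. Caseload rises either because more veterans enter or because each stays longer. Only the first lowers what VA pays per veteran helped. The planned measure treats the two alike.

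Actual stays could differ between groups even though the program is nominally 6 months everywhere. The Background says no case management model was required in aftercare and that practice varied by site, whereas CTI runs in timed phases ending in a transfer of care. Early exit, retention or overrun could each shift mean stay.

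What is at stake is the business case. This comparison is the only stated check on whether CTI has an additional delivery cost, which is the condition in footnote b. A flat monthly figure could leave a real per-veteran cost out of the balance, and an apparent saving could be credited to CTI when each veteran costs the same. A monthly rate also cannot be set against per-HEV offsets until it is multiplied by months enrolled.

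**Working it through.** The cost section gives no pay, caseload, intake or mean stay, so there is no plan figure to reproduce. All values below are assumptions chosen to show direction and size.

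**Identities.** Let S be monthly pay and benefits per case manager, a the entries per case manager per month, L the mean stay in months and C the mean caseload. With steady intake, C = a × L. Then:
- planned measure: S / C = S / (a × L)
- cost per veteran entering: S / a = (S / C) × L

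The two differ by the factor L.

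**Illustration: S = 7,000, mean stay 4 months versus 5 months.**

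| | Stay | Entries/month | Caseload | Monthly cost per HEV | Cost per veteran |
|---|---|---|---|---|---|
| Intake unchanged | 4 | 5 | 20 | 350 | 1,400 |
| | 5 | 5 | 25 | 280 (-20%) | 1,400 (0%) |
| Caseload unchanged | 4 | 5 | 20 | 350 | 1,400 |
| | 5 | 4 | 20 | 350 (0%) | 1,750 (+25%) |

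**Range.** The relative changes depend only on the ratio of stays, not on S, a or C.

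| Change in mean stay | Monthly cost, intake unchanged (cost per veteran flat) | Cost per veteran, caseload unchanged (monthly cost flat) |
|---|---|---|
| 5 to 6 months | 5/6 - 1 = -17% | 6/5 - 1 = +20% |
| 4 to 6 months | 4/6 - 1 = -33% | 6/4 - 1 = +50% |
| 6 to 9 months | 6/9 - 1 = -33% | 9/6 - 1 = +50% |

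**Where the planned measure works.** Hold stay at 6 months in both groups, index pay at 100 and let caseload fall from 12 to 10. Monthly cost goes from 100/12 = 8.33 to 100/10 = 10.00. Cost per veteran goes from 6 × 8.33 = 50 to 6 × 10.00 = 60. Both rise 20%, so an added cost through smaller caseloads is detected.

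**Definition of a veteran served in a month.** If anyone enrolled for part of a month counts, caseload is about a × (L + 1). With pay 100 and a = 2, stays of 4, 6 and 9 months give monthly costs of 10.0, 7.1 and 5.0. The direction is the same.

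**The per-entrant measure has its own blind spot.** With pay 7,000 and a full caseload of 20, a mean stay cut from 6 to 3 months by early exit raises intake from 3.33 to 6.67 a month. Cost per entrant falls from 7,000/3.33 = 2,100 to 7,000/6.67 = 1,050, while each veteran receives half the months of service. The monthly cost stays at 350.

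**The case against.** A reader might infer that the no-added-cost hypothesis is not tested at all. The document does not support that. It declares a test against matched control sites, and that test picks up the most direct way in which a structured model could raise delivery cost, namely fewer veterans per paid case manager.

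The bias also needs stays to differ between groups. Aftercare is a 6-month program for control sites too, CTI was tailored to 6 months, and the 6-to-9-month range describes CTI in general. At equal stays, cost per veteran is a constant multiple of the planned figure and the comparison is valid. This stands: a difference in stay is a possibility, and nothing in the document shows that one will occur. A nominal duration does not fix actual stays, though, and the plan would not reveal a difference if one arose.

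Cost per service-month is also a legitimate meaning of efficiency: in the first scenario the same payroll delivers 25% more veteran-months. That stands too, and it is why the monthly figure should be kept. Replacing it with cost per entrant would trade one blind spot for another, since cost per entrant falls when veterans leave early.

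Two smaller points hold. Calling the measure nothing but inverse caseload is exact only with a common pay estimate, because pay that varies by case manager or site would also move it. And a monthly rate can be converted to a per-HEV cost by multiplying by months enrolled, so the different units in the ROI section are not an error in themselves. The conversion does need mean stay, which this cost comparison does not name.

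**Conclusion.** The point holds in a limited form. The planned measure is a valid test for caseload effects and is incomplete for cost per veteran. If mean stay differs between CTI and control sites, it can show a saving when cost per veteran is flat, or no change when cost per veteran is higher. For stay differences of 4 versus 5 up to 4 versus 6 months, the spurious saving is 20% to 33% at constant intake, and the hidden rise is 25% to 50% at constant caseload. These sizes assume steady intake and a common pay level. The stays are illustrative, since the document gives none. If stays turn out equal, the planned comparison needs no correction. The stronger conclusions, that the hypothesis goes untested or that the measure should be replaced, do not follow. This is a cheap improvement to a cost outcome and does not affect the primary fidelity outcome.

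**What to change.** Keep the monthly cost per HEV as planned. Beside it, report for implementation and control sites:
- mean enrolled months per HEV;
- entries per case manager;
- case management cost per HEV entering aftercare, either as monthly cost times mean enrolled months or as case manager cost in months 6 to 18 divided by HEVs entering in that period.

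Use the per-HEV figure when judging whether CTI has an additional delivery cost under footnote b of Table 5, and when setting delivery cost against the per-HEV offsets in the ROI section. State that no single measure is to be read alone, because cost per entrant falls when veterans leave early and monthly cost falls when they stay longer.

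The cost is a little more analysis and a few lines of text. The rosters, aftercare entry dates and pay estimates are already to be obtained. One limitation should be stated: spending in months 6 to 18 also covers veterans who entered earlier. This affects both groups alike if intake is steady, and the version based on mean enrolled months avoids dividing that spending by entrants.
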